**Methods and analysis:**

This randomized cross-over study using a within-subjects test-retest design will enroll 32 infantry members of the Slovenian Armed Forces. To investigate the reliability and validity of the 30-15_IFT_ test, an incremental treadmill test (TR), a 2_MR_ test, and two identical 30-15_IFT_ will be performed in randomized order. Additionally, participants will be subsequently divided into two groups based on their score on the Army Physical Fitness Test (APFT), whereas differences in visual attention will be assessed by using the d2 test. The primary analysis will assess differences in key physiological outcomes between the different CRF tests (TR vs. 2_MR_ vs. 30-15_IFT_). In addition, the relative reliability of all dependent variables between two 30-15_IFT_ trials will be estimated by interclass correlation coefficient (ICC), while relationship between maximal oxygen uptake, heart rate and maximal running speed of 30-15_IFT_, TR and 2_MR_ will be assessed using Pearson’s correlation.

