## Materials and methods

### Study design

The proposed study is a part of a greater project entitled “Enhancement of Physical and Combat Preparedness of Slovenian Armed Force Members; “(original language, Slo: “Dvig telesne in bojne pripravljenosti pripadnikov Slovenske vojske”), which was funded by the Slovenian Research Agency (ARRS) and Slovenian Ministry of Defense (project No. V5-2106; project manager: Assoc. [name]. [name]; principal investigator: Assist. [name]. [name]). This is a randomized cross-over study using a within-subjects test-retest design. To test the current hypothesis, an incremental treadmill test (TR), a 2_MR_ test, and two identical 30-15_IFT_ will be performed in the population of SAF soldiers. For a better understanding of the following text, the term participant is used instead of soldier. The present study will be conducted over a maximum period of 2 weeks per participant. Participants will be instructed to visit the laboratory four times at least 72 h apart. At the first visit, they will be familiarized with the experimental procedures and asked to sign a written informed consent form to participate in the study. Then, participants will be randomly assigned to four experimental conditions (i.e., TR, 2_MR_ and two 30-15_IFT_ running tests).

Additionally, participants will be subsequently divided into two groups based on their score on the APFT (score ranging from 1 to 5). Thus, the higher-scoring group (HSG) is defined as an APFT score of ≥ than 4; and the lower-scoring group (LSG) is defined as an APFT score of ≤ than 2.

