#### Statistical analysis

All data will be presented as mean ± SD with 90% confidence interval limits (90% CI). All statistical analysis will be conducted using the SPSS statistical software (version 27.0, IBM Inc., Chicago, United States). Descriptive statistics will be used to summarize demographic characteristics of participants and outcomes. Normality od the data will be confirmed by using the visual inspection of histogram and Q-Q plot and analytically by Shapiro-Wilk test, while the homogeneity of variances of normally distributed variables will be tested by using Levene’s test.

Differences in key physiological outcomes between the different CRF tests (TR vs. 2_MR_ vs. 30-15_IFT_) will be assessed by One-Way ANOVA analysis. The relative reliability of all dependent variables between two 30-15_IFT_ trials will be estimated using the ICC, two-way random effects model (consistency type). ICC values will be classified as very high if > 0.90, high if between 0.70 and 0.89, and moderate if between 0.50 and 0.69. The following criteria will be used to declare good reliability: CV < 5% and ICC > 0.69 (Buchheit et al., 2011). In addition, the standard error of the estimate (SEM) and the coefficient of variation (CV) will be calculated as measures of absolute reliability, indicating the within-subject variation, as previously proposed (Hopkins, 2000). To further address the reliability of the data, bias and random error will be calculated, followed by the minimal detectable change (MDC). To test the usefulness of the IFT, the spreadsheet provided by Hopkins will be used (Hopkins). Usefulness will be determined by comparing the smallest worthwhile change (SWC) with the typical error of measurement (TE) and will be interpreted as follows: “Marginal” (TE > SWC), “OK” (TE = SWC) and “Good” (TE < SWC) (Hopkins, 2007).

Relationship between VO_2max_, HR_peak_ and end running speed of 30-15_IFT_, TR, and 2_MR_ will be assessed using Pearson’s correlation (r). Also, the relationship between VO_2max_ obtained from TR, 2_MR_, and 30-15_IFT_ will be investigated. The following thresholds of the correlation coefficient will be used to assess the magnitude of the relationships analyzed: weak ≤ 0.35; 0.36 ≤ moderate < 0.67; 0.68 ≤ high < 1 (Taylor, 1990).

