In addition, to determine performance differences between two groups of SAF members, a repeated-measures General Linear Model will be used for main physiological parameters estimated from different tests (TR vs. 2_MR_ vs. 30-15_IFT_) as within-subject factor, whereas groups (HSG vs. LSG) will be used as between-subject factors. Partial eta squared (η^2^) values of 0.01, 0.06, and 0.14 rated difference as small, moderate and high, respectively (Cohen, 1988). Statistical significance for all analysis conducted will be accepted at *p* ≤ 0.05.

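### Neither model named for TR vs 2MR vs 30-15IFT has a session term, so a drift over the four randomised sessions biases the test-type effect if the first or second 30-15IFT trial alone is used, and costs precision if the two are averaged

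*Protocol article*

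**What the plan says.** The Study design section states: "This is a randomized cross-over study using a within-subjects test-retest design". The abstract adds that TR, 2MR and "two identical 30-15_IFT_ will be performed in randomized order". Four sessions are planned: "Participants will be instructed to visit the laboratory four times at least 72 h apart". The time limit is also given: "The present study will be conducted over a maximum period of 2 weeks per participant". No balanced sequence scheme is described; the text says only that "participants will be randomly assigned to four experimental conditions (i.e., TR, 2_MR_ and two 30-15_IFT_ running tests").

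Two models are named for the three-test comparison in the Statistical analysis section. The first, for what the abstract calls the primary analysis, reads "Differences in key physiological outcomes between the different CRF tests (TR vs. 2_MR_ vs. 30-15_IFT_) will be assessed by One-Way ANOVA analysis". The second, for the comparison of higher- and lower-scoring groups, reads "a repeated-measures General Linear Model will be used for main physiological parameters estimated from different tests (TR vs. 2_MR_ vs. 30-15_IFT_) as within-subject factor", with HSG vs LSG as the between-subject factor. Neither contains session, period, sequence or order. A shift between occasions is considered only in the reliability analysis of the two 30-15IFT trials (consistency-type ICC and calculated bias). That is a different question from the three-test comparison.

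**The concern.** In a cross-over, randomised order keeps a session effect from favouring any one condition on average, provided each condition occupies the sessions alike. Here 30-15IFT is run twice and TR and 2MR once each, while the comparison has three levels. If one of the two 30-15IFT trials is selected by its rank in time, its average session is not that of TR or 2MR, however well the order was randomised.

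A session effect is plausible, though the article gives no size for one. On preparation it says "At the first visit, they will be familiarized with the experimental procedures", and no practice trial is described. The Participants section bars strenuous activity from 3 days before the first session and during the study. Learning, fatigue or detraining could each move results over four maximal efforts. At stake is whether a reported difference between 30-15IFT and the other tests belongs to the test or to when it was run. Replacing the One-Way ANOVA by a repeated-measures analysis with test type as the only within-subject term would not settle this.

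**Working it through.** The article gives no figure for this comparison. Its only computed sample size (6 subjects, for the ICC) has no bearing here.

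**Inputs from the article:** 32 participants; four sessions holding TR, 2MR, 30-15IFT and 30-15IFT; randomised order; significance at 0.05. **Assumed:** all orders equally likely, complete data, a linear drift of b within-person SD per session common to all tests, and no participant-by-test variation except where stated.

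**1. Average session of each test.** The two 30-15IFT trials occupy one of six equally likely pairs of sessions: (1,2), (1,3), (1,4), (2,3), (2,4), (3,4).
- First trial: (1+1+1+2+2+3)/6 = 10/6 = 1.67.
- Second trial: (2+3+4+3+4+4)/6 = 20/6 = 3.33.
- TR and 2MR: (1+2+3+4)/4 = 2.5 each.
- Mean of the two 30-15IFT trials: (1.67 + 3.33)/2 = 2.5.

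**2. Bias in 30-15IFT minus TR when no true difference exists.**
- First trial: (1.67 − 2.5)b = −0.83b, which is −0.17 SD at b = 0.2 and −0.42 SD at b = 0.5.
- Second trial: the same size with the opposite sign.
- Mean of both trials: 0.

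**3. Standard error of that difference without a session term.** Over the 12 orders, the session gap between the first 30-15IFT trial and TR has mean square 40/12 and mean −10/12, so its variance is 3.33 − 0.69 = 2.64. For the mean of both trials the gap has variance 2.5.
- First trial: SE = √[(2 + 2.64b²)/32].
- Mean of both: SE = √[(1.5 + 2.5b²)/32].

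| 30-15IFT value used | b | Formula SE | Simulated SE | Simulated bias | Type I error |
|---|---|---|---|---|---|
| First trial | 0 | 0.250 | 0.248 | about 0 | 5% |
| First trial | 0.2 | 0.257 | 0.254 | −0.17 | 10% |
| First trial | 0.5 | 0.288 | 0.287 | −0.42 | 29% |
| Mean of both | 0 | 0.217 | 0.215 | about 0 | 5% |
| Mean of both | 0.2 | 0.224 | 0.222 | about 0 | 5% |
| Mean of both | 0.5 | 0.258 | 0.255 | about 0 | 5% |

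The simulations used 4,000 runs per setting. With the mean of both trials, the SE rises by about 3% at b = 0.2 (0.222/0.215) and 19% at b = 0.5 (0.255/0.215). Adjusting each difference for its session gap removes the bias and holds type I error at 5% to 6%. The adjusted SE stays at 0.284 with the first trial only and at 0.218 with both.

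**4. The three-level repeated-measures F test.**
- First trial used, no true difference: rejection in about 6%, 11% and 28% at b = 0.1, 0.25 and 0.5.
- Two trials averaged: type I error stays near 5%. Power for a 0.7 SD difference in TR is about 87% at b = 0, 83% at 0.25 and 74% at 0.5.

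**5. The group analysis.** A drift shared by everyone, with order randomised in both groups, cancels from HSG vs LSG and from group-by-test. Simulated type I error for group-by-test was 4% to 5% in every setting, including first trial only.

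**6. The random part of a session-adjusted model.** A model with a participant effect alone, and both 30-15IFT trials given the same code, treats two runs of one test as no more alike than a shuttle run and a treadmill run. With no drift, its type I error was about 9% to 10% when participant-by-test variance was 1 to 2 times the residual variance (assumed). A session-adjusted analysis that allows for this variation held about 5%.

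**The case against.** The strongest case on the other side has four parts.

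- **The larger harm needs a choice the article does not make.** It never says that the first or the second 30-15IFT trial alone enters, and a condensed article may leave that to the full protocol. Averaging the trials, or choosing one at random, keeps type I error at about 5%. This stands. A reader might infer that the test comparison is biased as planned, but the documents support that only conditionally.
- **The drift is assumed.** A linear 0.25 to 0.5 SD per session means 3 × 0.25 = 0.75 to 3 × 0.5 = 1.5 within-person SD from session 1 to session 4. The spacing of visits, the bar on other strenuous activity and the briefing on each testing day all argue for less. At 0.1 SD per session the worst case is about 6%. This also stands and limits the size of the point.
- **The group model serves another question.** A reader might infer that the HSG vs LSG results are compromised. They are not biased by a shared drift; only the test-type effect is affected.
- **A repeated-measures GLM can be adapted.** A reader might infer that the named method cannot handle order at all. Order could enter as a between-subject factor, with its interaction with test carrying the session effect. That is costly with 12 possible orders and 32 participants, but not impossible. The models as stated do not include it.

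None of this supplies a session term or shows that one is unnecessary. Both models are named with their factors, so the point concerns what the article fixes, not detail left to an unseen analysis plan.

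**Conclusion.** The concern holds in a limited form. Both stated models omit session although its order is randomised. The test-type effect is biased by about 0.83 times the per-session drift if the first or second 30-15IFT trial alone represents the test. If the two are averaged, the loss is precision only: about 4 points of power at 0.25 SD per session (87 − 83) and 13 points at 0.5 (87 − 74). If there is no drift, nothing is lost. The figures rest on an assumed linear drift common to all tests, equally likely orders, 32 complete participants and no participant-by-test variation. The change is worth making because it is cheap and protects the primary comparison whichever trial is used. The missing participant term in the One-Way ANOVA is a separate matter.

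**What to change.** For TR vs 2MR vs 30-15IFT, replace both named models with a linear mixed model on all four sessions (the MIXED procedure in SPSS, the software already named):

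- fixed effects for test type (both 30-15IFT trials coded as 30-15IFT) and session number (1 to 4, categorical);
- a random participant effect and a random participant-by-test effect, so that the two 30-15IFT trials may correlate more closely than different tests do;
- group and group-by-test added for the HSG vs LSG analysis.

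Report session-adjusted test differences with confidence intervals. An alternative is to use the mean of the two 30-15IFT trials with session adjustment. Either route also settles how the two trials enter. Adjusting with a single trial is less attractive: with no drift it raises the SE from 0.248 to 0.284, against 0.215 to 0.218 with both trials.

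The cost is analysis wording only, since session order is known from the randomisation. The session term takes three degrees of freedom and about 1 to 2 points of power if there is no session effect. The participant-by-test component is one more variance to estimate and costs a little further. A common session term does not remove learning specific to one test, and the report should say so.

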## Strengths and limitations of this study

–This study will be the first to investigate the reliability and validity of the 30-15 Intermittent Fitness Test in military personnel.–This study will be the first to compare three different protocols for assessing cardiorespiratory fitness assessment in military personnel.–The study will provide the adopted formula for accurate estimation of maximal oxygen uptake (VO_2_max) for infantry members of the Slovenian Armed Forces (SAF) from the 30-15 Intermittent Fitness test.–The study will provide information about differences in visual attention between better and less physically prepared members of military personnel and its corresponding response following maximal endurance running test. This will enable better understanding of the importance of physical fitness for cognitively demanding situations like those at the battlefield.–A potential limitation of the study is that we will recruit greater number of male than female SAF members, as it is difficult to find an adequate number of female participants who meet the pre-specified inclusion criteria.

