### Participants

Thirty-two SAF infantry members (males, *N* = 27) will be recruited for the proposed study. Inclusion criteria are: age 18–40 years, both male and female SAF infantry members who are performing regular military tasks on daily basis, with no history of injuries in the last 6 months prior to recruitment, have not reported any musculoskeletal pain, with no history of chronic musculoskeletal, metabolic, pulmonary, neurological and cardiovascular diseases. Participants will be instructed to avoid any strenuous physical activity for at least 3 days prior to the start of the first testing session and during the course of study, which will be monitored by their superiors. They will be requested to refrain from consuming ergogenic substances and caffeinated beverages prior to the tests. Before the initial assessment on each testing day, a brief meeting will be held to explain the study protocol in detail.

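### The HSG versus LSG model has no age or sex term, so an unadjusted group difference, above all in visual attention, cannot be credited to physical fitness alone

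*Protocol article*

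**What the plan says.** **Group formation.** Under Study design, "participants will be subsequently divided into two groups based on their score on the APFT (score ranging from 1 to 5" points). HSG takes members with 4 or more points; at the other end, "the lower-scoring group (LSG) is defined as an APFT score of ≤ than 2". What is randomised is the running tests: "participants will be randomly assigned to four experimental conditions (i.e., TR, 2_MR_ and two 30-15_IFT_ running tests"). HSG versus LSG is therefore an observational contrast.

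**Model.** The last paragraph of Statistical analysis says that "to determine performance differences between two groups of SAF members, a repeated-measures General Linear Model will be used for main physiological parameters", with test (TR, 2-mile run, 30-15 IFT) as the within-subject factor, "whereas groups (HSG vs. LSG) will be used as between-subject factors". No covariate is named. Demographic characteristics are otherwise only summarised descriptively, and no matching or stratification by age or sex is described.

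**Population.** Under Participants, eligibility covers "age 18–40 years, both male and female SAF infantry members". Of the 32 to be recruited, 27 are male, which leaves five women.

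**Interpretation.** The Introduction expects better prepared members to lose less visual attention after a maximal run. Strengths and limitations says of the attention comparison: "This will enable better understanding of the importance of physical fitness for cognitively demanding situations like those at the battlefield".

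**The concern.** A contrast between groups that people sort themselves into by performance carries along whatever else differs between them. Age and sex are obvious candidates here: the sample spans 22 years of age and both sexes, and the article's own VO2max equation has a term for each. If the two groups differ in age or sex composition, the unadjusted difference mixes that composition with fitness.

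This matters most where the article makes a claim about fitness itself, namely visual attention. A reader told that fitter soldiers keep their attention better would want to know that the comparison is not, in part, one of younger with older members or of men with women. The group difference in aerobic measures raises a milder question, because there the stated aim is only to describe how the groups differ.

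The ICC analysis and the pooled correlations do not use the groups and are not affected.

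**Working it through.** The article gives no effect size or sample size for this contrast. Its only computed figure (6 subjects) is for the ICC and has no bearing here.

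**Inputs from the article**
- 32 participants, 27 men, so 32 − 27 = 5 women (Participants).
- VO2max formula (30-15 Intermittent fitness test): sex coefficient 2.15 in absolute value; age slope −0.741 + 0.058 × MRS per year. The sex coding is not given, so only the size of the sex term is used, for a one-unit difference between the sexes.

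**Assumptions**
- Equal groups of 16, 10 or 8. Sixteen per group requires that nobody scores 3, since that score belongs to neither group.
- Worst case for sex: all five women in one group.

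**1. Shift from sex composition at fixed running speed:** (5 / n) × 2.15.
- n = 16: 0.3125 × 2.15 = 0.67 ml/kg/min
- n = 10: 0.50 × 2.15 = 1.07 ml/kg/min
- Women balanced across groups: 0

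Assuming an SD of 4 to 6 ml/kg/min and a two-sided t-test, a shift of this size with no other group difference gives p ≤ 0.05 with probability 0.06 to 0.08 (16 per group) or 0.07 to 0.09 (10 per group), against a nominal 0.05.

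**2. Age.** The slope is zero at 0.741 / 0.058 = 12.8 km/h. At 18 km/h it is −0.741 + 0.058 × 18 = +0.303 per year, so an assumed 5-year gap in mean age gives 5 × 0.303 = 1.5 ml/kg/min. The sign is positive: at equal speed, the formula gives the older member the higher value. The formula shows that age enters, but it does not tell us in which direction the group contrast would be distorted.

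**3. What sex adjustment does to precision.** With all five women in one of two groups of n, the squared correlation between group and sex is 5 / (2n − 5), so the variance inflation is (2n − 5) / (2n − 10). If age and sex explain an assumed 20% to 40% of between-person variance, the ratio of adjusted to unadjusted standard error is √((1 − R²) × inflation).

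| n per group | Variance inflation | SE ratio, R² = 0.2 | SE ratio, R² = 0.4 |
|---|---|---|---|
| 16 | 27/22 = 1.23 | 0.99 | 0.86 |
| 10 | 15/10 = 1.50 | 1.10 | 0.95 |
| 8 | 11/6 = 1.83 | 1.21 | 1.05 |

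The smaller the groups, the larger the possible sex shift and the more likely it is that adjustment widens the interval.

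**4. Visual attention.** The documents contain no age or sex figure on the d2 scale. The ml/kg/min values above cannot be carried over, and the size of any distortion in d2 is unknown.

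**The case against.** The strongest reply is that the model paragraph asks a descriptive question about physiological parameters. The APFT includes the 2-mile run, so a difference in aerobic measures between the groups is close to built in. A lower-scoring group with more women or older members is still the less prepared group, and the unadjusted contrast describes it correctly. This stands for the physiological parameters: making the adjusted effect the main result there would change the question.

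It does not dispose of visual attention. The paragraph does not name d2, but the Introduction and Strengths and limitations attach the fitness interpretation to it. One can answer that the hypothesis concerns decline after running, so stable differences in level cancel within each person. That is partly right, but it does not remove a difference by age or sex in the decline itself.

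A further reply is that an article condenses the plan and covariates may be listed elsewhere. They may be; but the article does state this model's factors, and group is the only between-subject one.

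Three stronger readings are tempting and unsupported:
- **Women and older members will gather in LSG.** The article does not say whether the 1-to-5 score is normed by age or sex. If it is, the imbalance may be small. Members scoring 3 drop out of both groups, so fewer than five women may be compared.
- **Sex alone could account for several ml/kg/min.** That needs a marginal sex gap which the documents do not give. Their only figure is 2.15, conditional on running speed.
- **Adjustment would also sharpen the estimate, by 11% to 23% under R² of 0.2 to 0.4.** That holds only if the covariates are unrelated to group, which is the case without bias to remove. It cannot be claimed together with the worst-case imbalance.

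**Conclusion.** The point holds in a limited form. The groups are not randomised, the stated model has no age or sex term, both variables are available, and the article means to attribute group differences, chiefly in attention, to physical preparedness. An unadjusted HSG versus LSG difference cannot carry that attribution by itself, because part of it may be age or sex composition. That it actually is confounded has not been shown.

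On the article's own sex coefficient, the VO2max distortion is between 0 and about 0.7 (16 per group) or 1.1 ml/kg/min (10 per group). This is conditional on running speed and on the assumed group sizes. The age part depends on a mean age gap that nobody can know yet, and the d2 part cannot be sized from the documents. As a description of how the two groups differ physiologically, the unadjusted contrast is sound.

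**What to change.** In the last paragraph of Statistical analysis:

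1. **d2.** In any HSG versus LSG comparison of the d2 outcomes, both level and pre-to-post change, include age (continuous, centred) and sex as between-subject covariates. Base the statement about fitness on that adjusted effect.
2. **Physiological parameters.** Keep the unadjusted group contrast as the descriptive result and report the age- and sex-adjusted estimate beside it.
3. **Sensitivity.** Repeat the group comparisons in men only, because at most five women can contribute and the sex term will be poorly estimated.

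No new data are needed. The cost is two degrees of freedom and, if the women are concentrated in one group, possibly a wider interval (variance inflation 1.23, 1.50 or 1.83 with 16, 10 or 8 per group). The text should give reduced bias as the reason for adjusting and promise no gain in precision.

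### Effect-size labels meant for shares of total variance are applied to partial eta squared, so labels for the test and test-by-group effects grow with the between-test correlation

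*Protocol article*

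**What the plan says.** The Statistical analysis section says that "a repeated-measures General Linear Model will be used for main physiological parameters estimated from different tests". Test (treadmill, 2-mile run, 30-15) is the within-subject factor, and "groups (HSG vs. LSG) will be used as between-subject factors". The stated aim is "to determine performance differences between two groups of SAF members". Magnitude is then graded by one rule: "Partial eta squared (η^2^) values of 0.01, 0.06, and 0.14 rated difference as small, moderate and high, respectively". The rule is not limited to any one effect in the model. Significance is judged separately: "Statistical significance for all analysis conducted will be accepted at *p* ≤ 0.05".

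The Participants section recruits "Thirty-two SAF infantry members". Under Study design they are to be "divided into two groups based on their score on the APFT (score ranging from 1 to 5"). The higher-scoring group needs a score of at least 4, and "the lower-scoring group (LSG) is defined as an APFT score of ≤ than 2". A score of 3 falls in neither group, so the model may hold fewer than 32 people. The protocol does not say how many.

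**The concern.** Partial eta squared is effect SS divided by effect SS plus that effect's own error SS. For the test factor and the interaction, the error is the subject-by-test residual, from which stable differences between people have been removed. The more strongly the tests correlate, the smaller that residual and the larger the statistic, even if the test means stay equally far apart. The 0.01/0.06/0.14 scale grades a share of total variance, so it does not fit this statistic.

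This matters for a validity study because close agreement in ranking between tests is the result hoped for. The same section calls a correlation of 0.68 or more high. A successful validity result would therefore push the label for the difference between tests upwards, and a modest offset could be reported as a high difference. These labels are the only stated grading of magnitude for this model.

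**Working it through.** **Inputs.** From the protocol: cut-offs 0.01/0.06/0.14, k = 3 tests, two groups, N = 32 recruited. Assumed, because the protocol gives no figures: equal SDs, one common between-test correlation r (SD and r taken within groups), test means at −d/2, 0 and +d/2 in SD units, and all 32 people in the model.

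**1. Where the cut-offs come from.** With η² = f²/(1 + f²), f = 0.10, 0.25 and 0.40 give 0.0099, 0.0588 and 0.1379. The plan's figures reproduce, and they are total-variance benchmarks.

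**2. Size on the total-variance scale.** For these means f² = d²/6.
- d = 0.5: f² = 0.25/6 = 0.0417, and η² = 0.0417/1.0417 = 0.040, 'small'.
- d = 0.3: f² = 0.09/6 = 0.015, and η² = 0.015/1.015 = 0.015, 'small'.

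**3. Size as partial eta squared.** The population value is 3f²/[3f² + 2(1 − r)]. At d = 0.5 and r = 0.8 it is 0.125/(0.125 + 0.40) = 0.238, already past 0.14.

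**4. Chance of the label 'high'.** The test effect has 2 and 2(32 − 2) = 60 degrees of freedom. A partial eta squared of 0.14 corresponds to F = (0.14/0.86) × 60/2 = 4.88. The chance is that of a noncentral F(2, 60) exceeding 4.88, with noncentrality λ = 32 × 3f²/(1 − r). The last column, generalised eta squared, comes from simulating the sums of squares (20,000 data sets per row).

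| Spread of means | r | λ | Population partial η² | 'High' on partial η² | 'High' on generalised η² |
|---|---|---|---|---|---|
| 0.5 SD | 0.5 | 8.0 | 0.111 | 46% | about 1% |
| 0.5 SD | 0.68 | 12.5 | 0.163 | 71% | under 1% |
| 0.5 SD | 0.8 | 20.0 | 0.238 | 92% | under 1% |
| 0.3 SD | 0.7 | 4.8 | 0.070 | 24% | 0% |
| 0.3 SD | 0.8 | 7.2 | 0.101 | 41% | 0% |
| 0.3 SD | 0.9 | 14.4 | 0.184 | 79% | 0% |

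**5. No true effect, test or interaction.** Partial eta squared follows Beta(1, 30), so P(≥ 0.06) = 0.94^30 = 0.156 and P(≥ 0.14) = 0.86^30 = 0.011. On generalised eta squared the chance of reaching 0.06 is about 0%.

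**6. Group main effect.** Here the error term is the between-person variance, so the mismatch largely disappears. A true f = 0.10 has a population partial value of 0.015 at r = 0.5 and 0.011 at r = 0.9, still 'small'. With no true effect, P(≥ 0.06) = P(F(1, 30) ≥ 0.06/0.94 × 30 = 1.91) = 0.177.

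**The case against.** The strongest reply is that the model exists to compare the two fitness groups, and for that main effect the cut-offs are nearly appropriate. Comparison of the tests is assigned to a separate one-way ANOVA with no labels beside it. This stands as a limit on the point but does not remove it: the labelling rule is written for the whole model, which also yields the test and interaction effects.

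A second reply is that the inflation depends on a correlation found nowhere in the protocol. A reader might infer that any small difference between tests will be rated 'high'. The documents do not support that. For f = 0.10, the bottom of the 'small' range, the chance of 'high' at N = 32 is 8% at r = 0.5, 24% at r = 0.8 and 56% at r = 0.9, so it becomes the majority label only near 0.9.

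A reader might also infer that the repeated-measures design makes pure noise look 'moderate' in the group comparison. It does not. The roughly 1 in 6 chance at N = 32 is ordinary upward bias in a small sample, and generalised eta squared barely changes it for the group effect (17.7% to 14.5% at r = 0.8). About 30% would need only 20 people in the model, which is an assumption.

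Nor is the η² symbol an error, since the text names the partial form in words. Finally, means with SDs and 90% CIs are already planned, so readers would see original units. That softens the consequence, although an interval for each mean is not an interval for the difference between tests.

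**Conclusion.** The point holds for the test factor and the test-by-group interaction. The cut-offs and the statistic are on different scales, and the gap widens as the correlation rises. Over the correlations examined, a total-variance effect of 0.04 is labelled 'high' in 46% (r = 0.5) to 92% (r = 0.8) of trials, and one of 0.015 in 24% (r = 0.7) to 79% (r = 0.9). These figures rest on N = 32, equal SDs and a common correlation, none of which the protocol fixes for this model. The point does not extend to the HSG versus LSG main effect. No p-value, reliability criterion, correlation threshold or sample size uses the labels, so it is a minor correction to interpretation.

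**What to change.** In the Statistical analysis section, apply 0.01/0.06/0.14 to generalised eta squared for the test and interaction effects, with the denominator written out: effect SS / (effect SS + subject SS + error SS). Report the mean differences between tests in original units, with their 90% CIs, beside it. The labels should not be made conditional on p ≤ 0.05: that would tie a description of size to significance, and selecting on significance inflates the estimates that receive a label.

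The cost is one or two sentences. The sums of squares come from the model already planned, and no data collection changes. The downside is that reported effect sizes become smaller. Sampling error also remains: a true 0.04 can still pass 0.06 by chance, which is why the intervals in original units are needed.
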